# Comparison of immediate versus optional delayed surgical repair for treatment of acute anterior cruciate ligament injury through a parallel, multicentric, pragmatic randomized controlled trial – IODA trial

**DOI:** 10.1186/s13102-024-00816-6

**Published:** 2024-01-18

**Keywords:** Anterior cruciate ligament injury, RCT, Conservative therapy, ACL reconstruction

## Abstract

**Background:**

Standard care for anterior cruciate ligament (ACL) injuries often includes surgical reconstruction of the ACL. However, two randomized controlled trials [1, 2] (RCT) concluded that conservative treatment does not result in inferior clinical outcomes compared to immediate ACL reconstruction. More research is needed to verify these results and assess whether patient-specific parameters determine if a patient would benefit from one treatment option over the other.

**Methods:**

This is a pragmatic, multi-center RCT with two parallel groups. Patients with an acute ACL injury will be recruited from Belgian hospitals. Patients will be randomized to conservative treatment (rehabilitation + optional delayed surgery) or immediate ACL reconstruction (< 12 weeks). The primary outcome is the Knee injury and Osteoarthritis Outcome Score (KOOS) at 7 months (short term) and 1-year long term) post-injury. These following additional outcomes will be administered at 4 and 7 months (short term) and 1, 2, and 3 years post-injury (long term): patient-reported outcomes concerning knee symptoms, knee function and quality of life, functional knee tests, time to return to pre-injury activity level and return to work, structural knee joint damage and cartilage health (only at 4 months and 3 years post-injury), as well as adverse events such as re-rupture rates. Furthermore, the secondary objective is to identify (through a predictive analysis) individuals who would benefit the most from early reconstruction versus those who should rather be treated conservatively.

**Discussion:**

This large RCT will assess the clinical effectiveness of both surgical and conservative treatment. In addition, it will be the first study that provides insights into which patient-specific factors predict successful outcomes after conservative treatment of ACL injuries. These results will be the first step toward early patient identification regarding treatment decisions. This is urgently needed to avoid (1) delayed surgeries and prolonged rehabilitation and (2) unnecessary surgeries.

**Trial registration:**

this trial was registered on ClinicalTrials.gov (NCT05747079) on 10/02/2023.

**Supplementary Information:**

The online version contains supplementary material available at 10.1186/s13102-024-00816-6.

## Background

Rupture of the anterior cruciate ligament (ACL) is a common injury, especially in young, physically active individuals, with an indicate rate of 0.7/1000 person-years in Belgium [3]. The ACL has an important role in both static and dynamic stabilisation of the knee joint with a primary role limiting anterior translation of the tibia relative to the femur. In more than 70% of the injuries, the rupture occurs during a non-contact mechanism, such as a sudden change of direction or landing with the knee near full extension [4]. Frequently, not only the ACL is ruptured but typically also injuries to the menisci, cartilage, collateral ligaments and subchondral bone are present. The rupture of the ACL and damage to other knee stabilising structures, often results in knee joint instability affecting daily activities and sports leading to poor knee related quality of life. Furthermore, ACL injuries are associated with increased risk of post traumatic knee osteoarthritis (PTOA) [5] and athletes who return to sport have a high risk to sustain a re-injury [6]. The medical community has always been convinced that surgical repair of the ACL was necessary to restore mechanical knee stability so that patients can safely return to sports [7], but also to avoid long term disadvantages such as persistent knee instability, re-injury [6] and PTOA [5, 8]. However, evidence assessing treatment outcomes after ACL reconstruction does not support these beliefs. Ardern et al. [9] found that only 55% of athletes who underwent an ACL reconstruction return to their preinjury sport level. Furthermore, a recent meta-analysis showed that about 50% of the patients who underwent surgical repair of their ACL have cartilage degeneration 20 years after surgery [10] and up to 23% suffer a new ACL injury (ipsilateral or contralateral) within two years after return to sport [11]. Based on these results, one can assume that ACL reconstruction offers no certainty of restoration of normal knee function and protection from long-term disadvantages. Besides, it is uncertain whether ACL reconstruction results in benefits at all compared to conservative treatment. In total, 3 RCTs compared the clinical effectiveness between ACL reconstruction and conservative treatment (= rehabilitation + optional delayed surgery): the KANON trial [1] COMPARE trial [2] and ACL SNNAP [12]). The KANON trial concluded that a strategy of early reconstruction plus rehabilitation did not provide better results at five years than a strategy of initial rehabilitation with optional delayed ACL reconstruction [1, 13].The COMPARE trial found slightly better self-reported outcomes (knee symptoms, self-reported knee function, and perception of the ability to participate in sports) in the immediate ACL reconstruction group compared with the conservative group at two years follow-up. However, none of these findings were considered clinically important. The SNAPP trial investigated chronic ACL ruptures and found that patients with chronic symptomatic ACL deficiency have better clinical outcomes if they undergo surgery [12].

Based on the results of the KANON trial [1] and the COMPARE trial [2] one can conclude that conservative management with optional delayed surgery does not result in inferior clinical outcomes compared to immediate ACL reconstruction on a population level [14].

Though, on the level of the individual patient, large between-subject differences were found. In the KANON trial, 39% of the ACL patients in the conservative treatment group showed persistent knee instability requiring delayed surgery during the two years follow up, this percentage has grown to 51% at the five years follow up [1, 13]. The compare trial reported that 50% of the ACL patients in the conservative group required delayed surgery in the two years follow up [2]. In this group of patients, time to return-to-sport is extended, and longer sick leave times are observed because surgery is delayed compared to patients undergoing immediate ACL reconstruction [15]. Hence, early identification of patients who would benefit from early ACL reconstruction, or on the contrary, from rehabilitation alone, is crucial to reduce resource consumption and decrease irrelevant overtreatment. It is hypothesized that treatment success relies on clinical factors (such as knee function and MRI features [16] ) as well as the quality of rehabilitation [17], and psychological factors such as expectations [18], fear of re-injury [19, 20] and locus of control [21].

This large RCT has 2 aims: (1) to compare the clinical effectiveness of both treatment options and as such verify the existing literature, and (2) to assesses which patient-specific factors predict successful outcomes after conservative treatment of ACL injuries.

## Objectives

### Primary objective

The primary objective of this study is to compare the clinical effectiveness between immediate ACL reconstruction and conservative treatment with optional delayed surgical reconstruction of acute ACL injuries. Outcome parameters of interest are knee outcomes reported by the patients themselves. The primary outcome is the KOOS QOL.

This primary objective is translated in the following hypotheses:

The optional delayed surgery approach for acute ACL injury will result in non-inferior patient reported outcome measures at long term, i.e. 1 year post-injury, compared to immediate ACL reconstruction.The optional delayed surgery approach for acute ACL injury will result in better patient reported outcome measures at short term, i.e. 7 months post-injury, compared to immediate ACL reconstruction.

### Secondary objective

The secondary objective is to identify individuals who would benefit the most from reconstruction versus those who should rather be treated conservatively. A prediction model will be built in the intervention group (rehabilitation with optional delayed ACL reconstruction) to investigate this. Five predictor variables will be considered to predict whether delayed reconstruction is necessary. The following five variables will be considered:

KOOS QOL: patients with high scores on the KOOS QOL are less likely to require delayed ACL surgery [22].MRI features: patients with pathologic MRI features (fiber continuity disturbed, high/heterogenous signal intensity, more horizontal slope of ACL, unclear boundaries) are more likely to require delayed ACL surgery [16].hemarthrosis: patients with a lower degree of hemarthrosis detected by MRI are less likely to require delayed ACL surgery.IPQ-R (illness perception questionnaire): patients’ expectations play a crucial role in determining the success of non-surgical treatment [23].pre-activity level: patients who are less physically active prior to their injury are less likely to require delayed ACL surgery [24].

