#### Prediction analysis

A prediction model will be ran on the intervention group (rehabilitation with optional delayed ACL reconstruction). Based on 5 variables we want to assess whether it is possible to predict whether the patients in the intervention group will need surgery or not (binary outcome). The event of ‘delayed surgery’ was considered as binary outcome and not as time-to-event since the main question is to investigate whether it is possible to predict who will need a delayed surgery. The timing of the delayed surgery is less relevant as the timing is often influenced by several personal factors such as work, school, holiday and also by the availability of the surgeon etc.

A logistic regression model will be used and a backward selection procedure will be applied for model selection. The performance of the model will be quantified by the area under the ROC curve (AUC). Internal validation will be performed by means of a leave-one-out cross validation method to obtain a more realistic estimate of the model performance.

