## Discussion

Although two earlier RCTs (KANON [1] and COMPARE trial [2]) showed that conservative treatment with optional delayed surgery does not result in inferior clinical outcomes compared to immediate ACL reconstruction, most ACL patients in many countries still undergo immediate ACL reconstruction.

This lack of translation of research findings to clinical practice might be attributed to several reasons. One important reason is that evidence is still scarce as only 2 RCTs are performed (total of 288 patients were included). Furthermore, the fact that there are no evidence-based decision criteria that helps clinicians to decide on treatment choice, might let patients and physicians choose for surgery, to avoid potential conservative treatment failure and the associated prolonged rehabilitation.

Therefore, the first aim of this additional RCT, is to verify the results of the two previous RCTs in a large and pragmatic setting. We will aim to include 280 ACL patients, this sample size is twice as large as the population investigated in the previous RCTs. Second, this RCT will be the first adequately powered study to investigate whether patient-specific factors could predict which patients benefit from conservative treatment and which patients benefit from immediate ACL reconstruction. Early patient identification seems very important to further improve ACL treatment. In the first place, early classification will improve clinical outcomes and allow patients to return to work/sport more quickly. The patients who require surgery undergo timely surgery, and in this way, a double rehabilitation period is avoided. In addition, patients who are good candidates for non-surgical treatment do not undergo unnecessary surgery. There will be no additional iatrogenic trauma due to surgery, resulting in a faster return to pre-injury activities. Identifying patients early on also has the added benefit of reducing costs, as the most cost-effective strategy is to provide patients with optimal treatment as soon as possible. Eggerding et al. showed that rehabilitation and delayed surgery have the highest cost and potentially the longest trajectory to restore full function and should thus be avoided [41].

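### The secondary objective and the Discussion's power claim concern who benefits from which treatment, but the analysis assigned to them is a one-arm prognostic model of delayed surgery

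*Protocol article*

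**What the plan says.** All references are to the protocol article.

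- **Secondary objective:** "The secondary objective is to identify individuals who would benefit the most from reconstruction versus those who should rather be treated conservatively". The abstract's Methods repeat it with the word early: "individuals who would benefit the most from early reconstruction versus those who should rather be treated conservatively".
- **Method assigned to it**, in the same section: "A prediction model will be built in the intervention group (rehabilitation with optional delayed ACL reconstruction) to investigate this". The next sentence says that five predictors will be considered for whether delayed reconstruction is needed.
- **Prediction analysis:** "The event of ‘delayed surgery’ was considered as binary outcome and not as time-to-event", and "A logistic regression model will be used and a backward selection procedure will be applied for model selection". Performance is judged by the AUC with leave-one-out cross-validation.
- **Sample size:** the model is sized at 10 events per parameter for five predictors. Assuming that a third of conservative-arm patients have delayed surgery, this gives 150 patients in that arm.
- **Background**, second aim, worded more narrowly: "to assesses which patient-specific factors predict successful outcomes after conservative treatment of ACL injuries".
- **Discussion**, on power: "this RCT will be the first adequately powered study to investigate whether patient-specific factors could predict which patients benefit from conservative treatment". The sentence goes on to claim the same for patients who benefit from immediate reconstruction.

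**The concern.** Benefiting more from reconstruction than from conservative care is a difference between two outcomes for the same kind of patient, one under each strategy. Estimating how that difference varies with patient profile requires outcomes from both randomised arms. A model fitted only in the conservative arm, with delayed surgery as the response, says who tends to end up with surgery under that strategy. It does not say whether those patients would have done better, the same or worse with immediate reconstruction. Nor does it say that patients at low predicted risk would have gained nothing from it.

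The Background shows that the two questions can come apart. It reports delayed surgery in 39% to 51% of conservative-arm patients in two earlier trials, yet concludes that outcomes were not inferior at population level.

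At stake is the reading of the final report. With the objective and power claim as worded, a good AUC could be presented as evidence for choosing treatment, when it is evidence about prognosis under one strategy.

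**Working it through.** **1. The plan's own figure.** 5 predictors × 10 events = 50 events; 50 ÷ (1/3) = 150 patients. This reproduces exactly. Both inputs belong to a one-arm binary model, and neither a treatment difference nor its variation between patients enters the calculation.

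**2. Does any other planned analysis answer the between-treatment question?**
- The primary model (Primary outcome analysis) compares the arms on KOOS QOL with treatment group, visit and their interaction. It has no predictor terms.
- The secondary outcomes are analysed in the same way.
- The as-treated analysis uses a similar method, is declared exploratory and non-randomised, and does not involve the predictors.

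So the one-arm model is the only analysis that involves the five predictors, and it contains no treatment comparison.

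**3. What the trial could say about effect modification (illustration).**

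Inputs from the article: 130 and 150 randomised (Randomization); 10% drop-out, SD 19 for the KOOS QOL change at one year and a 7-point margin (Sample size). Evaluable: 130 × 0.9 = 117 and 150 × 0.9 = 135.

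Assumed, because the article gives none: a binary baseline factor with prevalence p between 1/3 and 1/2, and a two-sided 5% test.

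- SE of the treatment difference = 19 × √(1/117 + 1/135) = 2.40.
- SE of the interaction = 2.40 × √(1/p + 1/(1−p)). For p = 1/2 this is 2.40 × 2 = 4.80. For p = 1/3 it is 2.40 × √4.5 = 5.09.
- Power for a 7-point interaction: Φ(7/4.80 − 1.96) = 0.31 for p = 1/2; Φ(7/5.09 − 1.96) = 0.28 for p = 1/3.
- Interaction detectable with 80% power: 2.80 × 4.80 = 13.4 points for p = 1/2; 14.3 points for p = 1/3.
- Evaluable patients needed for 80% power at 7 points, in the planned allocation: about 930 (p = 1/2) to 1,050 (p = 1/3).

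Sensitivity: adjusting for baseline, with an assumed baseline-to-follow-up correlation of 0.5, multiplies the SE by √((1 + 0.5)/2) = 0.866. For p = 1/2 the SE becomes 4.16, the detectable interaction 11.6 points and the power at 7 points 39%.

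The variance of the interaction is 4 to 4.5 times that of the treatment difference. The 80% and 90% power stated for the primary tests therefore does not carry over to it.

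**The case against.** The best defence is that the article narrows the aim itself. The rest of the Secondary objective section speaks of predicting whether delayed reconstruction is needed. The Sample size and Prediction analysis sections define and size exactly that. The Discussion says that the trial will try to predict delayed reconstruction, so that clinicians can estimate the risk of failing non-operative treatment. The Background's second aim is also confined to conservative treatment. Delayed surgery after failed rehabilitation can arise only in the conservative arm, so a one-arm model is the natural tool. The benefit that the authors have in mind is largely the avoidance of a second rehabilitation period, longer sick leave and unnecessary surgery, and the article does not define the secondary objective in terms of KOOS QOL.

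Most of this stands. A reader might infer that the prediction model is misconceived, or that no form of the secondary aim can be met. The documents do not support that, because the model fits the narrower aim. A reader might also infer that the plan would assign patients to surgery by their score. It sets no such rule: the abstract calls the results a first step, and the Discussion describes risk information for a shared decision.

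What does not stand is the idea that the narrower passages cure the broad ones. The formal objective, the abstract and the power claim still state the contrast between treatments. Nor is the matter simply left to the analysis plan, because the objective itself names the one-arm model as its method. Whether patients at high predicted risk would do better with early surgery remains an assumption that the model does not test.

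**Conclusion.** The concern holds as a mismatch between the stated objective and power claim on one side and the assigned analysis on the other. The mismatch follows from the text and needs no numerical assumption.

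The figures of about 31% power at 7 points and about 13.4 points detectable with 80% power are an illustration. They rest on SD 19, 10% drop-out, one binary factor split 50:50 and KOOS QOL change as the measure of benefit. The split and that choice of measure are assumptions of this review, and several of the actual predictors are questionnaire scores. The figures show that the claim of adequate power does not extend to moderate effect modification. They do not show that a planned test is underpowered, because no interaction test is planned.

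A reader might also infer damage to the main result. There is none: the non-inferiority and superiority comparisons of KOOS QOL do not depend on the prediction model. This is a point about a secondary objective that should be fixed, chiefly by wording.

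**What to change.** **Rewording (sufficient by itself).** In the abstract's Methods, the Secondary objective and the Discussion, state the aim as predicting delayed reconstruction under an initial conservative strategy. Delete the claim of adequate power about who benefits, or limit it to what the 10-events-per-parameter rule covers. This costs only text.

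**If the between-treatment question is kept.** Add an analysis in all randomised patients, labelled exploratory: the treatment difference in 12-month KOOS QOL across the baseline predictors or across the predicted risk of delayed surgery, with confidence intervals. Three details matter:
- A difference specific to 12 months needs group-by-time-by-predictor terms in the repeated-measures model, or a separate 12-month model adjusted for baseline. Group-by-predictor terms alone are not enough.
- Baseline KOOS QOL is one of the five predictors and may also be a response in a model applied to all time points. It must not serve as both.
- The risk score is fitted in the conservative arm only. Cross-validated predictions should be used for those patients, since overfitting in one arm can bias the treatment-by-risk interaction.

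The article restricts none of the predictors to one arm: KOOS and IPQ-R are taken at baseline, the diagnostic MRI is retrieved from the record, and pre-injury activity is asked. The cost is therefore a few model terms and no new data. The drawback is that the interaction estimates will be imprecise and must be reported as such.

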## Methods/design

### Study design

This is a pragmatic, multi-center, randomized controlled trial with two parallel groups: [1] conservative treatment (consisting of rehabilitation + optional delayed surgery) and [2] immediate ACL reconstruction in patients with an acute ACL injury.

The protocol is conform the Standard Protocol Items: Recommendations for Interventional Trials (SPIRIT) guidelines [25] (the SPIRIT checklist is provided as Additional file 1).

### Participants

#### Eligibility criteria

Participants eligible for inclusion in this trial must meet all of the following criteria:

Rotational trauma to a previously non-injured knee for which medical advice was sought within 4 weeks after injury.Medical diagnosis of ACL insufficiency including MRI (both partial and complete ruptures).Minimum of 16 years.

Participants eligible for this trial must **not** meet any of the following criteria:

Participant has a history of a previous ACL injury or knee surgery to the index knee.Indication for acute surgery because of related injuries to the knee. (e.g. bucket handle meniscal tear that results in a locked knee or intra-articular fractures)Female who is pregnant or plans to become pregnant in the first 4 months of the trial, since MRI assessment cannot be performed.

#### Study setting

This study will be performed in several Belgian hospitals: University Hospital of Leuven, Clinique Saint-Luc Bouge, Jessa Ziekenhuis Hasselt,, and University Hospital of Liège. Patients will be recruited at the Department of Orthopaedics and the Department of Physical Medicine and Rehabilitation of the participating sites. Additionally, in order to ensure the requested sample size, more sites will be selected in the course of the study.

